#### *Cognitive function; Smartphone-based symbol digit modalities test (SDMT)*

The baseline date will be considered as the date of baseline data collection. The smartphone-based SDMT (Pham et al., 2021), is a smartphone adaptation of the cognitive test, the symbol-digit modalities test (SDMT) examines processing speed and sustained attention by primarily assessing complex visual scanning and tracking. The test comprises of pairing specific numbers with given geometric figures. Responses are given by pressing correct

option on the phone display. Total raw score is calculated as number of correct responses to the total number of all responses given in 90 seconds interval.

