#### □ **Cognitive Function**

- **Ho:** An activity tracking and JITAI will not improve cognitive function in people with long COVID compared to usual care six months after randomisation.
- **Ha:** An activity tracking and personalised JITAI will improve cognitive function in people with long COVID compared to usual care six months after randomisation.

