#### *Secondary Outcome(s)*

Secondary outcomes include a range of physical, cognitive, and psychosocial health domains relevant to long COVID. These include:

- Overall symptom burden, including self-reported symptom frequency, persistence, and new COVID-19 infections.
- Quality of life, capturing physical, mental, and functional well-being.
- Neurological and cognitive function, including assessments of memory, attention, and nervous system symptoms.
- Respiratory function, specifically breathlessness and its impact on daily activities.
- Mental health, assessing anxiety and depression.
- Pain, measured through self-reported intensity and impact.
- Self-management and self-efficacy, evaluating participants' confidence in managing their condition.

These outcome domains have been selected to reflect the LC-COS core outcome set, ensuring that the study captures key aspects of long COVID that affect daily life.

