### *App design and features*

To aid data collection the app also includes a series of validated instruments. As a result, in addition to logging a bout of PEM the app includes four 'sections' that participants will be requested to complete monthly: A 'symptom check in' to get a view of the month-by-month symptom load of participants. A 'brain-fog test' to assess cognitive function using the symbol digit modalities test. The remaining instruments will be split into two groups A and B, with

each group completed at a single point in time. Group A includes the Edinburgh Neurological Survey, the modified PEM questionnaire, and the SF12 quality of life assessment. Group B includes the MRC breathlessness scale, the EQ-5D-5L, PHQ4, the self-efficacy for long-term conditions, and the visual analogue pain scale. Data from each of the instruments will be stored in a GDPR-compliant data server. We also have the data server scan each participant's responses daily and send appropriate notifications to complete one of the four sections each week if responses are missing.

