### *Statistical methods*

All analyses will be conducted using Jamovi version 2.3.21. Data will be tested for normal distribution and homogeneity of variance to confirm parametric assumptions are met. Data will be presented in text and tables as means and 95% confidence intervals (CI) unless otherwise stated. Because of randomisation, we did not undertake analysis of baseline equivalence, since the null hypothesis must be true and any differences due to chance . Only participants who completed follow-up testing were included in analysis (i.e. per protocol analysis). The effect of the energy management intervention on main and secondary outcomes will be examined using two-way mixed-model ANOVA with condition (intervention or control) as the between-subjects factor and time (pre- and post-intervention) as a within subjects' factor. Alpha level will be reported as exact p values and not described dichotomously as 'significant' or otherwise as recommended by the American Statistical Association . We will express effect sizes from the ANOVA as partial eta-squared ( $\eta^2p$ ), with values of 0.01, 0.06, and 0.14 interpreted as small, moderate, and large, respectively . For categorical data, (DSQ-PEM questions 6-10) we will use McNemar's Test for paired samples (pre- to post- intervention), or Chi squared test for between group effects (intervention vs. control).

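### The SDMT scoring sentence, read literally, gives a proportion correct that cannot register a change in speed, although the protocol says the test measures processing speed

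*Protocol*

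**What the plan says.** In the protocol's Measurement tools section, the entry on the smartphone SDMT says that the test "examines processing speed and sustained attention by primarily assessing complex visual scanning and tracking". The same entry then defines the score: "Total raw score is calculated as number of correct responses to the total number of all responses given in 90 seconds interval". The protocol gives no other SDMT score, neither a count of correct answers nor a response time.

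Three other places depend on this score:

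- App design and features makes the SDMT the app's cognitive test: "A 'brain-fog test' to assess cognitive function using the symbol digit modalities test".
- Secondary Hypotheses, Cognitive Function, states that the intervention "will improve cognitive function in people with long COVID compared to usual care six months after randomisation".
- Statistical methods sends it to the same model as the other outcomes: "The effect of the energy management intervention on main and secondary outcomes will be examined using two-way mixed-model ANOVA", with condition and time (pre and post) as factors.

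**The concern.** In a test of fixed length, speed shows only in how many items a person gets through. A score that divides by that number discards it. The entry therefore names processing speed first among the things measured and then fixes a score that does not depend on speed.

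If an analyst follows the sentence as written, a participant who works faster at six months with the same error rate will show no change, and a slow, careful participant can outrank one who gives many more correct answers. A benefit of the intervention that took the form of faster processing would then be missing from the analysis of the cognitive-function hypothesis.

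**Working it through.** **No figure to reproduce.** The protocol gives no mean, SD, accuracy, effect size or power for the SDMT. The check is therefore the algebra of the scoring rule, followed by an illustration on assumed values.

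**Algebra.** Let *T* be the responses given in 90 seconds and *p* the share of them that are correct.

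- Number correct: *C = pT*, which rises with speed (*T*) and with accuracy (*p*).
- Score as literally worded: *C/T = pT/T = p*, from which *T* has gone.

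**Examples.**

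| Correct / given | Ratio | Number correct |
|---|---|---|
| 38 / 40 | 0.950 | 38 |
| 57 / 60 | 0.950 | 57 |
| 20 / 20 | 1.000 | 20 |
| 55 / 57 | 0.965 | 55 |

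The first two people tie on the ratio, although the second gives 57/38 = 1.5 times as many correct answers in the same time. The third ranks above the fourth on the ratio, with 20 correct answers against 55.

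**Illustration of power.** All inputs except the group sizes are assumptions. Responses given are normal with SD 10 and mean 40 in the control arm and 45 in the intervention arm, a speed gain of (45 − 40)/10 = 0.5 SD. The test is a two-sided t-test at 0.05 on follow-up scores. There are 85 per arm, the protocol's target before the drop-out allowance.

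With the same accuracy in both arms:

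| Accuracy, both arms | Power, count | Power, ratio |
|---|---|---|
| 80% | 0.83 | 0.05 to 0.06 |
| 90% | 0.88 | 0.05 to 0.06 |
| 97% | 0.89 | 0.05 to 0.06 |

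With 77 and 84 per arm, the completers in the protocol's demographics table, and accuracy of 95% in both arms, the count gives 0.88 and the ratio 0.05. A rejection rate of 0.05 is the false-positive rate, so the ratio carries no information on this effect. That does not depend on accuracy being close to 100%.

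With accuracy allowed to differ (85 per arm, individual accuracies drawn from a beta distribution with concentration 50):

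| Accuracy, control vs intervention | Speed gain | Power, count | Power, ratio |
|---|---|---|---|
| 96% vs 97% | 0.5 SD | 0.94 | 0.38 |
| 95% vs 97% | 0.5 SD | 0.96 | 0.89 |
| 92% vs 95% | 0.5 SD | 0.98 | 0.96 |
| 92% vs 95% | none | 0.13 | 0.96 |

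The two scores answer different questions. The ratio responds to accuracy only. The count responds mainly to speed under these inputs, and in the last row it largely misses an effect on accuracy alone.

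**Limit of the illustration.** The planned analysis is a pre/post mixed ANOVA, not a t-test on follow-up scores, so none of these figures is this trial's power. The qualitative result carries over: if *p* does not change, the ratio has no condition-by-time signal whatever happens to *T*.

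**The case against.** The strongest reply is that the sentence is badly worded rather than wrong. It does not say divided by, proportion or percentage, and calling the result a raw score fits a count, or a display of so many out of so many. This stands as a real possibility. It does not remove the point, because the sentence brings in all responses given, which a count does not need, and nothing else in the protocol settles the matter. On either reading the sentence has to be corrected.

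A second reply is that accuracy is itself a cognitive measure. The entry also names sustained attention, the hypothesis concerns cognitive function in general, and the secondary outcome domain reads "Neurological and cognitive function, including assessments of memory, attention, and nervous system symptoms", without mention of speed. This stands too, and it confines the mismatch to the processing-speed component.

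It could also be said that scoring belongs in an analysis plan. Here, however, the protocol did not leave the scoring open: it fixed a rule, and the rule conflicts with the construct given in the same entry.

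A reader might go further and infer that the cognitive hypothesis is bound to be reported as no effect whatever the truth. The documents do not support that. It holds only for an effect on speed with accuracy unchanged; where accuracy differs, ratio power in the illustration runs from 0.38 to 0.96. A reader might also suppose that accuracy on such a task sits near its ceiling, leaving the ratio no room to move. The protocol gives no accuracy data, so that cannot be claimed, and the point does not need it.

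**Conclusion.** The point holds in a limited form. As literally worded, the SDMT score is insensitive to the number of items completed, and so to processing speed, which the same entry says the test examines. It remains sensitive to accuracy, and a count may have been intended.

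The insensitivity to pure speed effects is exact and follows from the algebra. Its practical size is not known from the documents: on assumed inputs, about 0.83 to 0.89 power on the count against about 0.05 on the ratio when accuracy is equal in both arms, with the ratio rising as high as 0.96 when accuracy also differs.

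The reach is one secondary outcome. The DSQ-PEM analysis and the sample size do not use this score. The sentence should be corrected, but the main conclusion of the trial does not depend on it.

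**What to change.** Replace the scoring sentence with one that defines the SDMT score for the cognitive-function hypothesis as the number of correct responses in 90 seconds. Report proportion correct beside it as a supporting measure of accuracy, so that a gain in attention without a gain in speed is not lost. If a count was what was meant all along, say so and drop the reference to all responses given.

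The cost is one sentence, plus rescoring if the ratio has already been computed. Rescoring is possible only if the numbers of correct and total responses, or the item responses, were kept. App design and features says that instrument data are stored on a server but not at what level of detail, so this should be checked first. If only the ratio was kept, the report should describe the outcome as response accuracy and not as processing speed.

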#### *Pain Visual Analogue Scale (VAS)*

The baseline date will be considered as the date of baseline data collection. The VAS is a validated pain rating scale first developed by Hayes and Patterson (1921), and scores are recorded by dragging a mark on a 10-cm line that represents a continuum between ‘no pain’ and ‘worst pain’. The findings suggested that 100-mm VAS ratings of 0 to 4mm can be considered no pain, 5 to 44 mm, mild pain; 45 to 74 mm, moderate pain; and 75 to 100 mm, severe pain.

#### *The Edinburgh Neurosymptoms Questionnaire (ENS)*

The baseline date will be considered as the date of baseline data collection. ENS is a 30-item yes/no survey which include the addition of 241 yes/no sub-questions designed to assess the presence and nature of: blackouts, weakness, hemisensory syndrome, memory problems, tremor, pain, fatigue, globus, multiple medical problems, and operations (Shipston-Sharman et al., 2018).

#### *The Symptom Questionnaire (SQ)*

The baseline date will be considered as the date of baseline data collection. The SQ-48 is a 92-item yes/true/no/false questionnaire with brief and simple items state scales of depression, anxiety, anger-hostility, and somatic symptom (Kellner, 1987). Symptom subscales are added together and scored 1 when the answer is YES/TRUE.

## **STATISTICAL CONSIDERATIONS AND DATA ANALYSIS**

### *Sample size and statistical power*

To determine sample size, our primary outcome variable is the DSQ-PEM. Using previous work, a minimum clinically relevant difference can be estimated as a change of 13 points on a 100-point scale . Assuming a standard deviation (SD) of 25 , this resulted in a pairwise effect size of  $d=0.5$  (Cohen’s  $f=0.25$ ). We calculated our desired sample size for a two-way mixed-model (within- and between-subjects) analysis of variance (ANOVA). Using the WebPower package in R Studio, and the `wp.rmanova` function, with two groups, two time points, a medium effect size ( $f=0.25$ ), assuming sphericity, an alpha of 0.05, desired statistical

power of 0.9, testing for an interaction effect, the total n was 170 (85 per group). Consequently, we aimed to recruit 125 participants per group to allow for 30% drop-out.

### *Statistical methods*

All analyses will be conducted using Jamovi version 2.3.21. Data will be tested for normal distribution and homogeneity of variance to confirm parametric assumptions are met. Data will be presented in text and tables as means and 95% confidence intervals (CI) unless otherwise stated. Because of randomisation, we did not undertake analysis of baseline equivalence, since the null hypothesis must be true and any differences due to chance . Only participants who completed follow-up testing were included in analysis (i.e. per protocol analysis). The effect of the energy management intervention on main and secondary outcomes will be examined using two-way mixed-model ANOVA with condition (intervention or control) as the between-subjects factor and time (pre- and post-intervention) as a within subjects' factor. Alpha level will be reported as exact p values and not described dichotomously as 'significant' or otherwise as recommended by the American Statistical Association . We will express effect sizes from the ANOVA as partial eta-squared ( $\eta^2p$ ), with values of 0.01, 0.06, and 0.14 interpreted as small, moderate, and large, respectively . For categorical data, (DSQ-PEM questions 6-10) we will use McNemar's Test for paired samples (pre- to post- intervention), or Chi squared test for between group effects (intervention vs. control).

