## PARTICIPANT DEMOGRAPHICS

Supplementary table displaying participant characteristics of those who completed the study.

|              | Control (n=77)         | Intervention (n=84)    |
|--------------|------------------------|------------------------|
|              | Mean (95% CI)          | Mean (95% CI)          |
| Age (years)  | 47 (45-50)             | 45 (43-48)             |
| Gender (M/F) | 60 F (78%), 17 M (22%) | 66 F (79%), 18 M (21%) |

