## EMPLOYMENT STATUS AT BASELINE

[figure not shown][figure not shown]

Supplementary figure displaying the employment status of all participants at baseline. Not all participants completed the questionnaire, thus why the total n is not 125 per group.

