## BACKGROUND

People with long COVID report 'push-crash' cycles, with a disproportionate worsening of

symptoms in response to activity, similar to post-exertional malaise (PEM) reported by patients with chronic fatigue syndrome. These PEM-like symptoms increase the overall symptom load, reduce each individual's quality of life, and make recovery harder.

Adaptive pacing has emerged as a common strategy to self-manage PEM-like symptoms. Our systematic reviews suggest adaptive pacing is effective in improving some symptoms in people with ME/CFS. However, recent work endorsed by our long COVID PPI group indicates that implementing adaptive pacing is often problematic for those attempting to self-manage. Difficulties include accurately estimating concepts such as energy availability and predicted energy use and identifying and tracking a suitable threshold to limit activity. Combining these requirements to plan daily activities, often hour by-hour, can be highly challenging, particularly when symptoms include impaired cognition.

This project aims to determine if combining continuous activity tracking with a just-in-time adaptive intervention (JITAI) can address these limitations. JITAIs provide information to participants at a time and context where they can act upon it. Widely used in behaviour change research, JITAIs are yet to be applied to adaptive pacing. Using a randomised control study design, we will allocate 250 participants to receive either JITAI supported adaptive pacing or usual care. Our primary outcome is PEM using the De Paul Symptom Questionnaire (DSQ)-PEM at baseline and 6 months.

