## **STUDY DESIGN**

This study was designed as a pragmatic randomised controlled trial (RCT) to evaluate the effectiveness of an activity tracking and personalised just-in-time adaptive intervention (JITAI) for managing post-exertional malaise (PEM) in people with long COVID. A pragmatic RCT was chosen to assess the intervention in real-world conditions, with that findings are generalisable to routine clinical and self-management settings. Pragmatic trials consider diverse participant adherence, varied settings, and real-life constraints and this approach was intended to allow for a more comprehensive understanding of the intervention's feasibility, acceptability, and potential for real-world implementation.

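### The analysis set is restricted to participants who completed follow-up and labelled per protocol; it is a complete-case set, and it leaves the arm comparison unprotected by randomisation

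*Protocol*

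**What the plan says.** Statistical methods in the Protocol states the rule directly: "Only participants who completed follow-up testing were included in analysis (i.e. per protocol analysis". The main and secondary outcomes are then tested with a two-way mixed ANOVA with condition between subjects and "time (pre- and post-intervention) as a within subjects' factor". The Protocol names no other analysis set.

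On numbers, the Background says "we will allocate 250 participants to receive either JITAI supported adaptive pacing or usual care", and the sample-size section says "we aimed to recruit 125 participants per group to allow for 30% drop-out". The note to the employment figure reads "Not all participants completed the questionnaire, thus why the total n is not 125 per group", which implies that 125 per group was reached. The demographics table, headed "Supplementary table displaying participant characteristics of those who completed the study", gives 77 control and 84 intervention participants.

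On data collected, App design and features describes four app sections "that participants will be requested to complete monthly". The PEM questionnaire sits in instrument group A. The Randomisation section says that participants cannot be blinded.

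**The concern.** Two things are wrong with the stated rule.

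First, the label. A per-protocol set is defined by adherence to the assigned treatment. This set is defined by whether a follow-up score exists. Someone who ignored the tracker but answered the final questionnaire is in; someone who paced carefully but did not answer is out. A reader who trusts the label will take the result as an effect among adherers, which it is not.

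Second, the selection happens after randomisation. The same section relies on randomisation to say that any baseline difference is due to chance. That argument holds for everyone randomised, not for those who stayed. The arms also give different reasons to stay: one receives a tracker, live feedback and messages, the other questionnaires and reminders. If leaving is related to outcome, and differently so by arm, the difference goes straight into the primary estimate. The plan does not state the assumption that would rule this out.

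**Working it through.** **Inputs.** Target 125 per arm, 30% drop-out, 170 in total (85 per arm), power 0.9, alpha 0.05, f = 0.25 and a 13-point relevant difference: Sample size and statistical power. Completers 77 and 84: Participant demographics. That 125 per arm were actually randomised is an assumption: it is a target in two places and implied in a third.

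**Step 1. Reproduce the plan's sample size.** For the 2 x 2 interaction, use a noncentral F with lambda = f² x N, df1 = 1, df2 = N − 2.
- N = 170: lambda = 0.0625 x 170 = 10.63, power 0.8999. The first N at or above 0.90 is 171, so the stated 170 is reproduced to rounding.
- Drop-out: 85 / 0.70 = 121.4, so 122 per arm; the stated 125 covers it (125 x 0.70 = 87.5).

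**Step 2. Who is excluded.**

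| | Randomised (assumed) | Completers | Excluded |
|---|---|---|---|
| Control | 125 | 77 | 48 (38.4%) |
| Intervention | 125 | 84 | 41 (32.8%) |
| Total | 250 | 161 (64.4%) | 89 (35.6%) |

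The arm difference in exclusion is 38.4 − 32.8 = 5.6 percentage points. Its standard error is √(0.384 x 0.616/125 + 0.328 x 0.672/125) = 0.060, or about 6.0 points, so the difference is within chance.

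**Step 3. Power.** N = 161: lambda = 0.0625 x 161 = 10.06, power 0.884, against 0.90 planned. This is a small loss.

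**Step 4. Possible bias.** Let D be the mean improvement of completers minus that of non-completers within an arm. The completer mean exceeds the all-randomised mean by (fraction excluded) x D, so

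bias in the arm difference = 0.328 x D_int − 0.384 x D_ctl.

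The Protocol gives no value of D. Every value below is an assumption.

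| D_int | D_ctl | Bias (points) | Share of 13 |
|---|---|---|---|
| 5 | 0 | 1.64 | 13% |
| 10 | 0 | 3.28 | 25% |
| 20 | 0 | 6.56 | 50% |
| 0 | 10 | −3.84 | 30% |
| 10 | 10 | −0.56 | 4% |

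The bias depends on how far selection differs between arms, not on the exclusion rates alone. With similar selection in both arms it nearly cancels. With selection in one arm it does not, and it can go in either direction.

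**The case against.** Several stronger readings are tempting, and the Protocol does not support them.

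- *The randomised comparison is lost.* This goes too far. Arms are still compared as allocated. What is lost is the protection that randomisation gives against selection.
- *Dropout is shown to depend on arm and outcome.* It is not. The 5.6-point difference has a standard error of about 6.0, and nothing is reported on how leavers felt. It is a plausible risk in an unblinded trial with a self-reported outcome. Equal dropout rates would not remove that risk.
- *The rule contradicts the pragmatic design.* Study design says "Pragmatic trials consider diverse participant adherence, varied settings, and real-life constraints", but it sets no analysis population. Because the set is not defined by adherence, poor adherers with follow-up data are kept.
- *Baseline data are shown only for completers.* That is true of the age and sex table. The employment figure covers all participants at baseline.
- *The monthly scores would recover most of what is missing.* This is unproven. No dropout timing or monthly completion rate is given. The Background defines the primary outcome at baseline and six months only. The app section calls its PEM instrument a modified questionnaire, although it cites the same paper as the DSQ-PEM.

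Further limits stand. The exclusion percentages rest on an assumed denominator and on study completers being the DSQ-PEM analysis set. Exclusion above 30% is a result, not an error of planning. The Protocol promises a CONSORT flowchart and withdrawal reasons by arm, which is useful but descriptive. An SAP not at hand may contain sensitivity analyses, so their absence is not the finding. The finding is the rule that the Protocol states, which an SAP analysing everyone would contradict.

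**Conclusion.** The point holds. The Protocol positively fixes a completers-only set for the main and secondary outcomes and misnames it. If 125 per arm were randomised and the tabulated completers are the analysis set, about 36% are excluded. The estimate is then free of bias from dropout only if selection into completion is unrelated to outcome or cancels between arms, and the Protocol does not state that condition.

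Confidence is high on the rule and the label, good on the proportion excluded, and low on the size of any bias. The range of 3.3 to 3.8 points follows only from an assumed 10-point gap in one arm; 0.6 follows from the same gap in both. The power loss is not a reason to act. The exposure to selection is, because it bears on the primary estimate and can be reduced through the analysis.

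**What to change.** - Define the primary analysis set as all randomised participants with retained data, in their allocated arm.
- Fit a likelihood-based mixed model for repeated measures to every available DSQ-PEM score: baseline, the monthly PEM questionnaire where completed, and month 6. Include arm-by-month terms and take the month-6 arm contrast as the primary estimate. First confirm that the app's monthly instrument yields the same DSQ-PEM sum.
- Rename the present analysis complete-case and keep it as supportive.
- Add a delta-based sensitivity analysis that shifts missing month-6 scores separately by arm and reports how far the conclusion holds.
- Show age and sex for all randomised participants whose data are retained, beside the completers.

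The cost is analysis wording and some extra programming, with no new participants or visits. There are three limits. The model relies on data being missing at random given the observed scores, which is why the delta analysis is needed. People with only a baseline score add little. Data deleted on request, as Ethical considerations provides, cannot be recovered; the number of such requests should be reported by arm.

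### The planned two-time mixed ANOVA is a valid change-score test but less precise than baseline adjustment, and its power basis leaves open which SD the 25 is and what correlation is assumed

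*Protocol*

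**What the plan says.** Protocol, *Statistical methods*: main and secondary outcomes are examined with a "two-way mixed-model ANOVA with condition (intervention or control) as the between-subjects factor and time (pre- and post-intervention"). No baseline covariate is included, and the effect size to be reported is partial eta-squared. This section does not say which term of the model is the primary test.

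Protocol, *Sample size and statistical power*, identifies that term. The sizing variable is given as "To determine sample size, our primary outcome variable is the DSQ-PEM". The target is "a minimum clinically relevant difference can be estimated as a change of 13 points on a 100-point scale", followed by "Assuming a standard deviation (SD) of 25", from which the text derives d = 0.5 and f = 0.25. The calculation is for "two groups, two time points, a medium effect size", "assuming sphericity, an alpha of 0.05" and "power of 0.9, testing for an interaction effect, the total n was 170 (85 per group"). Recruitment is set at 125 per arm to allow for 30% drop-out.

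No correlation between the baseline and 6-month scores appears in the document, and the SD of 25 is not identified as the SD of a single-time score or of a change.

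**The concern.** The interaction in a two-arm, two-time ANOVA uses the baseline score as a second outcome rather than as a covariate. That raises two questions.

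- **Precision.** Baseline DSQ-PEM is already collected, and the planned model does not use it as efficiently as it could. The cost is a wider interval for the treatment effect on the primary outcome and on every continuous secondary outcome.
- **Basis of the power statement.** The noise in the interaction test is the SD of change. If 25 is the SD of a score at one time, going from 13/25 to an interaction effect size requires a correlation, and none is stated. The reader then cannot tell whether the 90% follows from the stated inputs.

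**Working it through.** **Inputs.** From *Sample size and statistical power*: difference 13 points, SD 25, d = 0.5, f = 0.25, alpha 0.05, power 0.90, 170 in total. From *Statistical methods*: two-by-two mixed ANOVA, completers only. From *Participant demographics*: 77 control and 84 intervention completers. The correlation ρ is not in the document, so it is treated as an assumption and varied.

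**1. The protocol's own figure.** For the interaction, take a noncentral F with 1 and n − 2 degrees of freedom and noncentrality n·f². At n = 170 the noncentrality is 170 × 0.0625 = 10.625 and power is 0.8999. Solving for 0.90 gives n = 170.06. The stated 170 is therefore right for f = 0.25. Drop-out is also covered: 85/0.7 = 121.4, so 122 per arm are needed, and 125 × 0.7 = 87.5.

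**2. What the interaction tests.** With two times, the interaction contrast is the difference between arms in mean change, and its F is the square of the two-sample t on change scores. A check on simulated data gave 10.0758 by both routes.

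**3. What f = 0.25 implies.** Equating n·f² with the squared noncentrality of that t-test, (n/4)(13/SD_change)², gives f = 13/(2·SD_change). So f = 0.25 means SD_change = 13/0.5 = 26. Sphericity holds automatically with two times and supplies no correlation.

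**4. The two readings of SD 25.**

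- *SD of change.* The standardised difference is 13/25 = 0.52. Power at 85 per arm is 92% (90% with the rounded 0.5). No correlation is needed.
- *Single-time SD, equal at both times.* SD_change = 25·√(2(1 − ρ)). Requiring this to be at most 26 gives ρ ≥ 1 − 676/1250 = 0.459. With the rounded d = 0.5 (12.5 points) the requirement is ρ ≥ 0.50. With the 87.5 per arm expected after drop-out, the threshold for 13 points is 0.44.

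**5. Comparison with baseline adjustment.** The ANCOVA residual SD is 25·√(1 − ρ²), ignoring the one degree of freedom spent on the covariate. The variance ratio to the change score is (1 − ρ²)/(2(1 − ρ)) = (1 + ρ)/2.

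Under the single-time reading, for 13 points and 85 per arm (noncentral t; the sample sizes use the normal approximation):

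| ρ | SD of change | Power, planned test | Power, ANCOVA | Variance ratio | n per arm for 90%: planned / ANCOVA |
|---|---|---|---|---|---|
| 0 | 35.36 | 66% | 92% | 0.50 | 156 / 78 |
| 0.2 | 31.62 | 76% | 93% | 0.60 | 125 / 75 |
| 0.3 | 29.58 | 81% | 94% | 0.65 | 109 / 71 |
| 0.4 | 27.39 | 87% | 96% | 0.70 | 94 / 66 |
| 0.46 | 25.98 | 90% | 97% | 0.73 | 84 / 62 |
| 0.5 | 25.00 | 92% | 97% | 0.75 | 78 / 59 |
| 0.7 | 19.36 | 99% | over 99% | 0.85 | 47 / 40 |

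The interval narrows by the square root of the variance ratio: √0.65 = 0.81, √0.75 = 0.87 and √0.85 = 0.92, or about 19%, 13% and 8% narrower. The ratio does not depend on which SD 25 is, only on equal SDs at the two times. If the SDs differ (s0 at baseline, s1 at 6 months), the change-score variance exceeds the ANCOVA variance by (s0 − ρ·s1)², which is never negative.

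**6. At the reported completer counts (77 and 84).** Under the single-time reading the planned test has 79% power at ρ = 0.3 and 88% at ρ = 0.46. The lowest ANCOVA power for ρ ≥ 0 is 90.6%, reached at ρ = 0.

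**The case against.** **The planned test is sound.** Under randomisation the interaction is an unbiased test of the treatment effect, and the sizing calculation matches the analysis model. This stands: the point concerns precision and documentation, and a reader who inferred bias or an invalid test would go beyond the document. The gain from adjustment also shrinks as ρ rises.

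**No power shortfall is shown.** A reader might infer that the trial is underpowered, or that its 90% requires ρ of at least 0.46. The document does not support either as a flat statement. It speaks of a change of 13 points and then of an SD without saying which SD, and the cited source is not at hand. If 25 is the SD of change, the 90% holds with no correlation. If it is a single-time SD, a ρ of 0.5 or more also suffices, and nothing in the document says how stable DSQ-PEM is over six months. What remains is that the interaction effect size cannot be derived from what is written.

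**ANCOVA does not guarantee 92% power.** It is tempting to say that 170 patients give at least 92% whatever ρ is. That assumes a 6-month SD of 25 and 85 per arm. If the 6-month SD were 30 (an illustrative assumption), ANCOVA power at ρ = 0.3 would be 84%, since 30·√(1 − 0.09) = 28.6.

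**A late change is not free of risk.** The document already reports completer numbers and a results figure, so altering the primary model may be post hoc. This stands and shapes the fix.

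**Conclusion.** The point holds in two parts of different strength.

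- **Precision: firm.** The planned interaction has at least the variance of a baseline-adjusted comparison. With equal SDs the adjusted variance is 35%, 25% and 15% lower at ρ = 0.3, 0.5 and 0.7.
- **Power statement: conditional.** The 170 is correct for f = 0.25, but the step from 13/25 to that f is undocumented. On the single-time reading, 90% at 85 per arm rests on ρ of roughly 0.44 to 0.50, depending on rounding and completer numbers. On the SD-of-change reading it stands as written. The document does not settle which applies.

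This is a change that should be made. It does not invalidate the trial.

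**What to change.** 1. In *Statistical methods*, for the primary and continuous secondary outcomes, replace the mixed ANOVA with ANCOVA of the 6-month score on arm and baseline score, plus the factors actually used to stratify randomisation. The equivalent baseline-adjusted repeated-measures model would also serve. First reconcile the two descriptions of randomisation: *Study implementation* names age and sex as stratification factors, while *Study procedure* mentions balance on gender only.
2. Report the adjusted mean difference in points with its 95% CI, to be read against the 13-point target, alongside partial eta-squared.
3. In *Sample size and statistical power*, say which SD the 25 is, state the assumed ρ (or the SD of change), and give power over a range of ρ. Any ANCOVA power figure, such as about 92% or more at 85 per arm for ρ ≥ 0, must state that it assumes a 6-month SD of 25.
4. If outcome data have already been seen, date the change, label it as made after that point, and report the planned ANOVA as well.

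The cost is rewording two paragraphs and, if item 4 applies, one additional reported analysis. No further data collection is needed.
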